#### Exclusion criteria

Participants will be excluded from the study if they present with the below exclusion criteria:

HADS depression subscale score >10.Significant visual impairment, homonymous hemianopia or visual-spatial neglect (stroke cohort only) as self-reported.Uncontrolled hypertension.Diagnosis of other neurological problems (e.g., Parkinson’s disease, multiple sclerosis, etc.).Language and communication deficits impairing the ability to express thoughts (e.g., aphasia).Has participated in a clinical drug trial in the past 6 months.Has an acute musculoskeletal injury that prevents participation in a structured exercise programme (eg, lower limb fracture).Is currently or has within the past 8 weeks received falls/balance/vestibular and/or cognitive rehabilitation.Has an implanted electrical medical device or cardiac pacemaker.Diagnosis of unstable Meniere’s or more than four migraines/month at the time of participating in the study (vestibular cohort only).

#### Sample size

The target sample size across all sites is 460. This equates to 60–100 participants per clinical site, with 30–50 participants recruited to intervention group (IG) and CG study arms, per clinical site, in line with recommendations for pilot feasibility studies.^49 52 53^

#### Recruitment

Each clinical site will recruit participants via (1) web-based advertisements, (2) social network groups, (3) relevant local patient bodies (for stroke, MCI, balance/dizziness problems, long covid), (4) specialist consultants and/or (5) research staff. Potential participants will undergo a telephone screening session with a researcher to determine their eligibility, with eligible participants booked in for baseline testing with the blinded outcome assessor. Participants will provide written informed consent (online supplemental appendix 1) upon arrival at their baseline outcome assessment session.

#### Randomisation and blinding

Participants’ will be randomised using an online platform (www.sealedenvelope.com), and opaque envelopes, into either the HT-IG, LT-IG or CG to undergo a HEP. Participants will not be able to choose their preferred group and must be willing to participate in the assigned group. Details of the randomisation procedure, eligibility screening and intervention procedure can be found in figure 3.

**Figure 3 F3:**
[figure not shown]
Flowchart of randomisation procedure and clinical flow of participants through the TeleRehaB DSS RCT. ax, assessment; ABC, Activities-Specific Balance Confidence Scale; CG, control group; DHI, Dizziness Handicap Inventory; eHeals, eHealth Literacy Assessment; EQ5D, EuroQuol-5 dimensions; FES, Functional Electrical Stimulation; FGA, Functional Gait Assessment; FSS, Fatigue Severity Scale; HADS, Hospital Anxiety and Depression Scale; IG, intervention group; MDPQ-16, Mobile Device Proficiency Questionnaire-16; Mini-BESTest, Mini-Balance Evaluation Systems Test; MoCA, Montreal Cognitive Assessment; PIS, Participant Information Sheet; RAPA, Rapid Assessment of Physical Activity; SCQ, Situational Characteristic Questionnaire; STAM-14, Senior Technology Acceptance and Adoption Model-14; SUS, System Usability Scale; SVV, Subjective Visual Verticality; TeleRehaB DSS, TeleRehabilitation Decision Support System; UEQ, User Experience Questionnaire; WEMWBS, The Warwick-Edinburgh Mental Wellbeing Scale.

This is a single-assessor blinded RCT. As this study is comparing a technology intervention (TeleRehaB DSS) versus standard care, it is not possible to blind the participants or the treating clinicians to the intervention provided.

### Intervention

#### Intervention group: TeleRehabilitation Decision Support System (high-tech and low-tech intervention arms)

Participants randomised into the TeleRehaB DSS IG will undergo a second randomisation into either the (1) high-tech group or (2) low-tech group.

The HT-IG will receive all components of the TeleRehaB DSS, consisting of a depth camera, lightweight AR headset that displays the hologram, inertial measurement unit (IMU) body-worn sensors, to record movement, a chest heart rate monitor and smartwatch for activity monitoring (figure 4). The AI-DSS will suggest multisensory balance exercises, including cognitive training and exergames delivered by AR. The platform also provides real-time feedback on individual’s performance based on collected IMU data, which are analysed using an EDGE computer processing unit. The LT-IG will receive a basic version of TeleRehaB DSS, with a depth camera, tablet and IMU sensor monitored exercises with real-time feedback, multisensory balance exercises and cognitive games, but without the exergames, smartwatch, mobile phone or AR.

**Figure 4 F4:**
[figure not shown]
Diagram of the TeleRehabilitation Decision Support System (TeleRehaB DSS) high-technology arm (**A**) and low-technology arm (**B**) hardware. In the high-technology arm (**A**), participants use a head-mounted augmented reality (AR) device; four inertial measurement units (IMUs) placed on both ankles, head and trunk; a depth-sensing camera for full-body motion capture; a smartwatch for additional physiological data and an ECG monitor worn on the chest. In the low-technology arm (**B**), participants use a tablet for exercise display, the same four IMUs and ECG monitor, and the depth camera for motion capture.

The TeleRehaB DSS includes an extended version of the HOLOBalance rehabilitation programme delivered via an AR hologram of a virtual physiotherapist. It is based upon established, evidence-based MBR protocols that have been shown to improve balance control in older adults at risk of falls and in persons with vestibular disorders.^23 54 55^ Additional exercises have been added to the TeleRehaB DSS, including range of motion stretching exercises and optokinetic stimulation exercises for participants with visual induced dizziness. Please see online supplemental material table S2 for exercise details and progression levels.

IG participants will be visited by a research team member to instal the TeleRehaB DSS into their home and taught how to use the system, with a practice session. The initial set of exercises will be set by the treating clinician and all subsequent exercise progressions will be suggested by the AI-DSS and either approved or disapproved by the treating clinician. The approved exercise programme will be loaded into the participant’s training plan which will automatically be deployed.

Participants will be required to complete the programme 5 days per week over 9 weeks. They will be encouraged to complete the programme in one session per day, but if required due to fatigue and/or scheduling issues, may complete the session in multiple bouts within a 24-hour period. Participants will be required to wear the equipment when performing the prescribed exercises. At the end of the study, a subset of participants will be invited to participate in a semistructured exit interview to discuss their experience using the TeleRehaB DSS system. This qualitative feedback on acceptability and usability will help to inform future iterations of the platform, for a larger-scale RCT and eventual adoption into local healthcare systems.

#### Control intervention: OTAGO home exercise programme; Meniere’s Dizziness programme

CG participants will receive a standard of care balance rehabilitation HEP; stroke and MCI participants will complete the *OTAGO HEP*^56^,^58^ (accessible at https://www.livestronger.org.nz/assets/Uploads/acc1162-otago-exercise-manual.pdf), while vestibular and long covid participants will complete the *Balance Retraining Booklet*^59 60^ (accessible at https://www.meandve.org.uk/files/pdfs/Balancing_Retraining_(Nov_2023).pdf).

Participants will be required to log their exercises daily on a written diary. The exercises will be reviewed remotely by the treating clinician every 3 weeks. Participants will also be required to complete a falls diary (online supplemental material table S2), which will be reviewed in the weekly telephone call. Exercises will be progressed in line with the recommendations from the OTAGO HEP and/or Meniere’s Dizziness booklet, in combination with the treating clinician’s clinical judgement.

### Outcome measures

All study participants will attend two sessions at the clinical site: at baseline (week 0) and post-intervention (week 10), where a blinded outcome assessor will collect outcome measure data. Participants will be asked to complete a subjective questionnaire set, walking/balance tests, a verticality perception test and a cognitive screen. These will take approximately 1.5 hours, including comfort breaks. Participants’ e-health literacy will only be collected at baseline, while system usability score (SUS) and User Experience Questionnaire (UEQ) will be collected post-intervention among the IG only.

The outcome assessor will be asked to record any incidences of unblinding and detail how this occurred. Due to the nature of this study, we do not foresee circumstances where emergency unblinding of the outcome assessor is required.

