#### Primary outcome measures

Primary outcomes of feasibility, acceptability, usability and safety will be investigated alongside clinical measures of Functional Gait Assessment (FGA) and EuroQol five-dimensional descriptive system (EQ-5D-5L) instrument pre-intervention and post-intervention. The FGA includes 10 tasks that assess dynamic and complex gait (eg, walking with head turns or stopping and turning), with a minimal detectable change (MDC) of 4.2 points in stroke populations and 6 points in vestibular disorders^61^ and minimally clinically important difference (MCID) of 4 points in community-dwelling older adults.^62 63^

Programme effectiveness will be evaluated using quality-adjusted life years (QALYs) measured with the EQ-5D-5L instrument.^64^ The EQ-5D-5L is a standardised, valid and reliable measure of health status for clinical and economic appraisal.^64^ The respondent is asked to rate their health status on five dimensions (mobility, self-care, usual activities, pain/discomfort, anxiety/depression), followed by a self-rated health score from 0 to 100. MCID ranges from 0.03 to 0.52.^65^,^67^

Primary outcomes are as follows:

*Acceptability*: recruitment (percentage of eligible participants enrolled); dropout rates; intervention adherence (percentage of prescribed sessions completed) monitored automatically through the system for TeleRehaB DSS participants and via an exercise diary for control groups.*Safety*: participants will be monitored for adverse event’s via completion of adverse events forms on the system database, during telephone or face-to-face contacts as part of the intervention phase and during follow-up assessments. Falls diaries will be collected weekly from participants during the intervention, and monthly for up to 6 months after completion of the intervention.*Feasibility*: protocol deviation (PD) or study protocol implementation problems (eg, logistical).*Usability*: participants’ experience using the system (perceived benefits, frustrations and recommendations) will be explored via exit interviews for all TeleRehaB DSS group completers. These participants will also complete the SUS^68^ and UEQ^69^ to explore system usability and user experience, respectively.

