#### Secondary outcome measures

Various secondary outcome measures will be used to assess clinical outcomes, programme effectiveness, system performance, AI model predictive power, e-health literacy and user experience. Please see table 2 for the detailed schedule of assessments.

**Table 2 T2:** Schedule of assessments for all participants enrolled in the TeleRehaB DSS study

		Screening	Baseline	Week 0	Weekly	Weeks 3 and 6	Post-intervention (week 10)	Monthly
Recruitment procedures	PIS informed consent	X	X					
Data collection and outcome measures	Demographics		X					
	HADS	X					X	
	DHI	X					X	
	FGA	X					X	
	MoCA	X					X	
	EQ-5D-5L		X				X	
	RAPA		X				X	
	ABC		X				X	
	Mini-BESTest		X				X	
	SVV		X				X	
	WEMWBS		X				X	
	FSS		X				X	
	SVQ		X				X	
	Exit interviews						X	
User experience measures	SUS						X	
	UEQ						X	
eHealth literacy measures	eHEALS		X					
	STAM-14		X					
	MDPQ-s		X					
Home-based interactions	Equipment installation and practice session (*IG only*)			X				
	Equipment de-installation (*IG only*)						X	
	Telephone call				X			
	Remote programme review					X		
	Perform HEP				X			
	Submit falls diary				X			X
	Submit exercise log				X			

ABC, Activities Specific Balance Confidence Scale; DHI, Dizziness Handicap Inventory; eHEALS, eHealth Literacy Assessment; EQ-5D-5L, EuroQol five-dimensional descriptive system; FGA, Functional Gait Assessment; FSS, Fatigue Severity Scale; HADS, Hospital Anxiety and Depression Scale; HEP, home exercise programme; IG, intervention group; MDPQ-s, Mobile Device Proficiency Questionnaire - short; Mini-BESTest, Mini-Balance Evaluation Systems Test; MoCA, Montreal Cognitive Assessment; PIS, Participant Information Sheet; RAPA, Rapid Assessment of Physical Activity; STAM, Senior Technology Acceptance and Adoption Model-14; SUS, System Usability Scale; SVQ, Situational Vertigo Questionnaire; SVV, Subjective Visual Verticality; TeleRehaB DSS, TeleRehabilitation Decision Support System; UEQ, User Experience Questionnaire; WEMWBS, The Warwick-Edinburgh Mental Wellbeing Scale.

Cost-effectiveness by means of the incremental cost-effectiveness ratio (ICER; the difference in mean costs divided by the difference in mean QALYs at the time of recruitment to the study and 1 year before the study and 1 year after the end of the intervention).

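### As written, the intervention-only SUS and UEQ fall within the blinded assessor's week-10 data collection, leaving an avoidable route to unblinding before the FGA is scored

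*Protocol article*

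**What the plan says.** The Randomisation and blinding section states "This is a single-assessor blinded RCT" and adds that neither participants nor treating clinicians can be blinded. The assessor is therefore the only masked party, and the article's strengths list credits the assessor-blinded design with strengthening internal validity.

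The Outcome measures section has every participant attend the site at baseline and at "post-intervention (week 10), where a blinded outcome assessor will collect outcome measure data". It then describes the session content: questionnaires, walking and balance tests, a verticality test and a cognitive screen. The same paragraph closes by saying which instruments are specific to one time point. E-health literacy is taken at baseline only, and "system usability score (SUS) and User Experience Questionnaire (UEQ) will be collected post-intervention among the IG only". The next paragraph asks the assessor to record any unblinding and how it came about.

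Under Primary outcome measures, usability is a primary outcome. Of the TeleRehaB DSS completers it says "These participants will also complete the SUS", together with the UEQ. The same section names "clinical measures of Functional Gait Assessment (FGA) and EuroQol five-dimensional descriptive system (EQ-5D-5L) instrument pre-intervention and post-intervention" alongside the feasibility outcomes.

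Table 2 marks SUS, UEQ, exit interviews and FGA in one week-10 column. SUS and UEQ stand under a user-experience heading, and exit interviews under data collection and outcome measures. The intervention-only "Equipment de-installation" is in the same column but in a separate block for home-based contacts.

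**The concern.** A system-usability form is given only to people who used the system, so its presence marks an intervention participant and its absence marks a control. If that form passes through the hands of the person who scores the gait test, the masking fails through the schedule itself and not through a chance remark.

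FGA, Mini-BESTest and MoCA are scored by the assessor and involve judgement. The Discussion says openly that better balance is expected in the intervention arms, so any drift by an unmasked assessor would most plausibly favour the technology. The trial is also meant to supply sample size estimates for a definitive trial (Trial design), so a distorted FGA difference would carry forward into that planning. The EQ-5D-5L is self-reported by participants who know their arm, so assessor masking does not protect it and this point does not bear on it.

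**Working it through.** The plan gives no figure to reproduce on this point. The check is to set the statements side by side and ask what each one fixes.

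1. **Who collects at week 10?** Outcome measures names one collector for the site session, the blinded assessor. No other collector of outcome data at that session is named anywhere in the article.
2. **Are SUS and UEQ part of that collection?** They appear in the paragraph that describes the two site sessions, alongside the instruments taken at baseline only. Primary outcome measures counts usability among the primary outcomes, so the two forms are naturally read as outcome measure data. Table 2 places them outside its home-based block. The natural reading puts them in the assessor's session, but the sentence is passive and names no collector.
3. **Do they come before the FGA?** No order is stated. The session description mentions questionnaires before the walking tests, but as a list and not as a sequence. A site that worked through the list in that order and gave all questionnaires together would reveal the group before the FGA, Mini-BESTest and MoCA were scored. Nothing in the text prevents this.
4. **What would be revealed?** Intervention versus control. Both technology arms complete the same two forms, so the forms alone need not separate high-tech from low-tech.
5. **Which assessments are exposed?** Week 10 only. According to the Figure 2 caption, baseline testing precedes randomisation.
6. **What safeguard is stated?** Recording of unblinding by the assessor. This documents a loss of masking but does not prevent it.

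**Scale, as illustration only.** The Sample size section gives 30–50 per site in each of the intervention and control groups, so 460 implies about 460 / 2 = 230 per group. Assume 20% loss, giving 230 × 0.8 = 184 assessed per group, and an FGA standard deviation of 5. Neither figure is in the document. The 95% confidence interval half-width for the between-group difference is then

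1.96 × 5 × √(2/184) = 1.02 points.

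With a standard deviation of 4 it is 0.82, and with 6 it is 1.23. A purely hypothetical scoring drift of 1 point would give, at a standard deviation of 5, an interval of 1.00 ± 1.02, or −0.02 to 2.02. This shows how precise the comparison might be. It says nothing about how large any drift would be.

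**The case against.** The strongest reply is that the article never says that the assessor touches these forms. They are completed by participants, Table 2 lists them under their own heading, and the week-10 column is a time point and not a single session, since equipment de-installation sits in it too. If the forms come after the tests, go to another team member or are filled in online, the FGA score is unaffected. Who hands over a form, and when within a visit, is operational detail that a journal article commonly leaves to the full protocol. Figure 3, which carries the clinical flow, is not shown.

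Most of this stands, and it limits the claim. A reader might infer that the schedule actually reveals allocation to the person scoring the FGA, potentially for all participants. The document does not support that, because it would need both the collector and the order, and neither is stated. A reader might also infer that a 1-point drift would by itself look like an effect. The arithmetic does not support that either: at the assumed standard deviation of 5 the interval still includes zero, and 1 point is well below the 4-point minimally important difference quoted for the FGA. Nor does any section place the exit interview in the assessor's session.

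The reply does not remove what the text does state: one named collector who must stay blinded, and two arm-specific forms listed in the same collection. That is a matter of wording present in the article, not of detail left out.

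**Conclusion.** The point holds as an avoidable unblinding route. As worded, Outcome measures assigns week-10 outcome collection to the blinded assessor and lists two intervention-only forms within it, with no preventive separation stated. If the assessor handles or sees them before scoring, intervention-versus-control status is exposed for the FGA, Mini-BESTest and MoCA at week 10.

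The conclusion rests on the natural but not the only reading of that paragraph. Whether unblinding would occur, how often, and how much it would shift the FGA cannot be derived from the document. The half-widths shown depend on an assumed standard deviation and an assumed loss rate, and the drift is hypothetical. This is a cheap improvement to the plan and not evidence that the outcome data are compromised. If the full protocol already separates the tasks, one clarifying sentence settles the matter.

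**What to change.** State in Outcome measures and in Table 2 that SUS, UEQ and exit interviews are collected by a team member other than the blinded assessor and are kept from the assessor's view. Two practical routes are the intervention-only equipment de-installation contact, already scheduled at week 10, or online self-completion. If a site cannot separate the roles, the minimum is that these items are given only after all assessor-scored tests for that participant are completed and locked. Keep the existing record of unblinding incidents as a check that the separation works.

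The cost is schedule wording and a site instruction. The article does not say who carries out de-installation or when it falls relative to the clinic visit, so sites using that route should confirm that the person and timing suit. Moving the forms out of the clinic session may make them slightly later or less complete. This matters because usability is itself a primary outcome, so their return should be tracked.

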#### Primary outcome measures

Primary outcomes of feasibility, acceptability, usability and safety will be investigated alongside clinical measures of Functional Gait Assessment (FGA) and EuroQol five-dimensional descriptive system (EQ-5D-5L) instrument pre-intervention and post-intervention. The FGA includes 10 tasks that assess dynamic and complex gait (eg, walking with head turns or stopping and turning), with a minimal detectable change (MDC) of 4.2 points in stroke populations and 6 points in vestibular disorders^61^ and minimally clinically important difference (MCID) of 4 points in community-dwelling older adults.^62 63^

Programme effectiveness will be evaluated using quality-adjusted life years (QALYs) measured with the EQ-5D-5L instrument.^64^ The EQ-5D-5L is a standardised, valid and reliable measure of health status for clinical and economic appraisal.^64^ The respondent is asked to rate their health status on five dimensions (mobility, self-care, usual activities, pain/discomfort, anxiety/depression), followed by a self-rated health score from 0 to 100. MCID ranges from 0.03 to 0.52.^65^,^67^

Primary outcomes are as follows:

*Acceptability*: recruitment (percentage of eligible participants enrolled); dropout rates; intervention adherence (percentage of prescribed sessions completed) monitored automatically through the system for TeleRehaB DSS participants and via an exercise diary for control groups.*Safety*: participants will be monitored for adverse event’s via completion of adverse events forms on the system database, during telephone or face-to-face contacts as part of the intervention phase and during follow-up assessments. Falls diaries will be collected weekly from participants during the intervention, and monthly for up to 6 months after completion of the intervention.*Feasibility*: protocol deviation (PD) or study protocol implementation problems (eg, logistical).*Usability*: participants’ experience using the system (perceived benefits, frustrations and recommendations) will be explored via exit interviews for all TeleRehaB DSS group completers. These participants will also complete the SUS^68^ and UEQ^69^ to explore system usability and user experience, respectively.

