**Figure 1 F1:**
[figure not shown]
Screenshots of (**A**) physiotherapist avatar and (**B**) representative exergame from the TeleRehab DSS. TeleRehab DSS, TeleRehabilitation Decision Support System.

Exercise data will be collected automatically in TeleRehaB DSS dashboard for the HT-IG and LT-IG, whereas CG participants will be required to log their exercise data manually in a diary provided. Exercises will be prescribed and progressed according to participant feedback and task performance, as assessed by the treating clinician. All treating clinicians will receive appropriate training prior to trial onset.

This study will compare acceptability of the TeleRehaB DSS programme (adherence, recruitment and dropouts) compared with current standard of care (OTAGO or Balance Retraining Booklet), which are commonly used in balance and vestibular rehabilitation. This study will also explore trends for effectiveness across several validated clinical outcome measures to identify whether a future trial is warranted and if so, to provide sample size estimates. The protocol has been developed using the Standard Protocol Items: Recommendations for Interventional Trials reporting guidelines^50^ and the flow of participants through the trial will be recorded in compliance with the Consolidated Standards of Reporting Trials statement^51^ (figure 2).

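### Adherence is recorded by a different method in each group and recruitment is fixed before randomisation, so neither supports the planned acceptability comparison with standard care

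*Protocol article*

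**What the plan says.** The Trial design section (text below Figure 1) commits to a comparison: "This study will compare acceptability of the TeleRehaB DSS programme (adherence, recruitment and dropouts) compared with current standard of care". The Primary outcome measures section lists the same three items under acceptability.

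**Adherence.** The sources are stated consistently in three places:
- Trial design, for the intervention arms: "Exercise data will be collected automatically in TeleRehaB DSS dashboard for the HT-IG and LT-IG".
- Trial design, for controls: "whereas CG participants will be required to log their exercise data manually in a diary provided".
- Control intervention: "Participants will be required to log their exercises daily on a written diary".
- Primary outcome measures, covering both: "intervention adherence (percentage of prescribed sessions completed) monitored automatically through the system for TeleRehaB DSS participants and via an exercise diary for control groups".

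**Recruitment.** Primary outcome measures defines it as "recruitment (percentage of eligible participants enrolled". On timing, the Recruitment section says: "Participants will provide written informed consent (online supplemental appendix 1) upon arrival at their baseline outcome assessment session". The Figure 2 caption puts allocation after baseline testing. Randomisation and blinding says that participants cannot choose a group and must be willing to take the one assigned.

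**Analysis.** The Statistical analysis section plans descriptive summaries of adherence, compliance and dropout.

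**The concern.** A between-group comparison needs a quantity that exists in each group and is measured in the same way in each.

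Adherence exists in each group but is not measured in the same way. A session performed without working or worn equipment may not reach the system. A diary can be filled in generously, or not returned. Participants are unblinded. The text describes no common measure and no cross-check between the two sources.

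Recruitment does not exist by group at all, because it is complete before the groups are formed.

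At stake is a primary outcome. A reader could take a difference in recording for a difference in acceptability and carry it into the design of the definitive trial, which is the third stated aim.

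**Working it through.** There is no stated figure to reproduce. The check sets the passages side by side and adds one illustration.

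**Recruitment**
1. The order of events is telephone screen, then consent on arrival at baseline, then baseline testing, then randomisation (Recruitment; Figure 2 caption).
2. The rate is number enrolled divided by number eligible. Both counts are made before allocation, from a single stream of people who must accept any arm.
3. The denominator cannot be divided by arm. If the numerator were divided after allocation over the shared denominator, the ratio of the two rates would simply be the allocation ratio. The contrast carries no information about acceptability.

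**Adherence**
1. Source in HT-IG and LT-IG: the system dashboard. Source in CG: the written diary. No group is described in the text as having both, so method and group cannot be separated. HT-IG against LT-IG is not affected in this way, since both use the dashboard.
2. Prescribed sessions, from the Intervention section: 5 days × 9 weeks = 45. A 10-point recording error is therefore 0.10 × 45 = 4.5 sessions.
3. Illustration. All of these inputs are assumptions: true adherence 70% in both groups; system captures a share c of sessions, 0.85 to 1.00; diary over-reports by o points, 0 to 10. Apparent difference (intervention minus control) = 70c − (70 + o).
   - c = 1.00, o = 0: 70 − 70 = 0
   - c = 0.95, o = 5: 66.5 − 75 = −8.5
   - c = 0.85, o = 10: 59.5 − 80 = −20.5
4. The reverse case applies the same 0.85 to the diary (missing entries or unreturned diaries) with complete system capture: 70 − 70 × 0.85 = 70 − 59.5 = +10.5.
5. With equal true adherence, the apparent difference therefore runs from −20.5 to +10.5 points. The range includes zero. The documents give no capture rate or diary error that would narrow it or fix its sign.

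**Dropout** arises after randomisation, and no arm-specific source is stated for it. It can be compared by arm.

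**The case against.** The strongest case on the other side is this. The first aim is to determine the acceptability of the system, with no comparator named. Adherence is only to be described, and no test or progression threshold depends on it. Recruitment is defined as a single percentage, and only one parenthesis in Trial design puts it among the things to be compared. The strengths and limitations box already concedes that home use of technology may affect adherence and data completeness. All arms get weekly calls, and Table 2 lists a weekly exercise log without restricting it to controls.

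Much of this limits the force of the point without removing it. The comparison is stated in Trial design and echoed in the strengths and limitations box, and a descriptive contrast can mislead as well as a tested one. The recruitment part is indeed a matter of wording and easily corrected. The rate also says something about acceptability, since entrants must be willing to receive TeleRehaB; it just cannot say it by arm. The Table 2 log is an ambiguity: the text assigns the diary to controls, so a common log may or may not exist.

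Two stronger readings are tempting and are not supported.
- **Recruitment close to 100% by construction.** A reader might infer this because FGA and MoCA appear among the criteria while consent comes at the baseline visit. But Table 1 makes FGA an alternative criterion in every cohort, MCI has no MoCA threshold, and the Recruitment section already calls people eligible after the telephone screen. The near-100% rate needs a denominator that the protocol does not state.
- **A recording artefact many standard errors wide.** That would need an assumed standard deviation, an assumed error size and errors that all push one way, and it would measure damage to a test that is not planned.

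**Conclusion.** The point holds in a limited form. The recruitment part is exact and needs no assumption: there is one trial-level value and no arm-specific one. The adherence part is that the two percentages can be calculated but cannot be compared without confounding by recording method. The size and sign of that bias are unknown. The range of −20.5 to +10.5 points shows only what modest errors could do under the stated assumptions and is not an estimate for this trial. Because the planned analysis is descriptive, the consequence is a possibly misleading description of a primary outcome, with no formal test at risk. The sample size is unaffected.

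**What to change.** 1. **Adherence.** Base the between-arm comparison on one instrument used in all arms, for example days exercised out of days prescribed, asked in the weekly call every participant already receives. State whether the Table 2 exercise log applies to all arms.
2. **System logs.** Report them as an intervention-only measure. Show agreement between log and self-report descriptively, and do not use it to correct control diaries: only intervention participants are sensor-monitored, so their reporting behaviour need not carry over.
3. **Recruitment.** Remove it from the between-arm comparison. Report it once for the whole trial, with those eligible at telephone screening as the denominator and baseline-visit screen failures shown separately.
4. **Acceptability by arm.** Compare post-randomisation uptake (started the allocated programme; withdrew on learning the allocation) and dropout.

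The cost is one standard question in an existing call and some rewording. The downsides are a small extra reporting burden in the intervention arms and residual self-report bias in unblinded participants, including recall problems that may be greater in the MCI cohort. The question has to be in place while participants are exercising, since it cannot be asked afterwards.
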